## Abstract

**Background:**

The serious negative health consequences of heavy drinking among adolescents is cause for concern, especially among adolescents aged 15 to 20 years with a low educational background. In the Netherlands, there is a lack of alcohol prevention programs directed to the drinking patterns of this specific target group. The study described in this protocol will test the effectiveness of a web-based brief alcohol intervention that aims to reduce alcohol use among heavy drinking adolescents aged 15 to 20 years with a low educational background.

**Methods/design:**

The effectiveness of the What Do You Drink (WDYD) web-based brief alcohol intervention will be tested among 750 low-educated, heavy drinking adolescents. It will use a two-arm parallel group cluster randomized controlled trial. Classes of adolescents from educational institutions will be randomly assigned to either the experimental (n = 375: web-based brief alcohol intervention) or control condition (n = 375: no intervention). Primary outcomes measures will be: 1) the percentage of participants who drink within the normative limits of the Dutch National Health Council for low-risk drinking, 2) reductions in mean weekly alcohol consumption, and 3) frequency of binge drinking. The secondary outcome measures include the alcohol-related cognitions, attitudes, self-efficacy, and subjective norms, which will be measured at baseline and at one and six months after the intervention.

**Discussion:**

This study protocol presents the study design of a two-arm parallel-group randomized controlled trial to evaluate the effectiveness of the WDYD web-based brief alcohol intervention. We hypothesized a reduction in mean weekly alcohol consumption and in the frequency of binge drinking in the experimental condition, resulting from the web-based brief alcohol intervention, compared to the control condition.

**Trial registration:**

Netherlands Trial Register NTR2971

## Background

Heavy alcohol use among adolescents continues to be a great public health concern in most Western countries, given the immediate and long-term health consequences [1]. In the Netherlands, the prevalence of heavy drinking is particularly high among adolescents with a low educational background, aged 15 to 20 years [2-4].

Adolescents with a low educational background not only engage in heavy drinking more often, but also start drinking at a younger age compared to higher educated peers [4-6]. Possible explanations for this difference are that they spend more time with friends, are raised more often in single-parent families, experience less rule setting and monitoring by the mother, and engage more often in externalizing behaviors [3].

Both early drinking onset and heavy drinking can place low-educated adolescents at an increased risk for developing acute and long-term health consequences, such as alcohol-related violence [7], drunk driving, injuries and risky sexual behavior [8]. This behavior is also associated with brain impairment and neurocognitive deficits, which have implications for learning and intellectual development [9,10]. In the long term, heavy drinking is predictive of, among other things, problematic adult alcohol use [11], liver cirrhosis [12], specific types of cancer, and cardiovascular disease [1]. From a public health viewpoint, it is crucial to develop alcohol prevention programs directed at adolescents with lower education levels to encourage them to change their risky drinking practices, especially considering that 60% of all adolescents, following secondary education in the Netherlands, are low-educated [3]. The study described in this protocol will test the effectiveness of the WDYD web-based brief alcohol intervention that aims to reduce alcohol use among heavy-drinking adolescents aged 15 to 20 years with a low educational background.

The school system in the Netherlands comprises several types of education. After eight years of primary education, pupils go directly to secondary education, which consists of preparatory secondary vocational education (VMBO), senior general education (HAVO), and preuniversity education (VWO). Pupils with a VMBO diploma are able to attend a secondary vocational education (MBO), which has four learning routes: 1) the theoretical route allowing admission to MBO or HAVO, 2) a mixed educational route, 3) the vocationally oriented route, and 4) a vocational route allowing pupils to enter the labor market directly. HAVO prepares pupils for higher professional education (HBO), while VWO prepares pupils for university.

In the Netherlands, there is a lack of evidence-based alcohol prevention programs targeting adolescents following the lower education levels [13,14]. The existing programs are mainly concentrated on first- and second-year MBO pupils, while less attention is paid to third- and fourth-year MBO pupils, partly due to the increasing difficulty of reaching them as a consequence of their internship commitments [14]. Moreover, the prevention programs are inadequately tuned to the influence of the direct social environment (that is, friends, peers and parents) that is related to the heavy drinking patterns of this specific target group [3]. Therefore, it is essential to develop and evaluate the effectiveness of alcohol prevention programs aimed at adolescents following the lower education levels.

Prior research has demonstrated that web-based brief alcohol interventions can be effective in reducing heavy alcohol use in adolescents and students [15-21]. Interventions delivered electronically via the internet have large practical advantages compared to the more conventional methods [22-24]. The internet is easily accessible and particularly appealing to young people. Furthermore, it allows the participants to access the intervention in the privacy of their homes at a convenient time, which may enhance their feelings of anonymity. Brief interventions are especially easy to implement by creating links on websites or providing the link of this website in promotion and education materials. Moreover, these interventions can be provided in an automated, cost-effective and flexible way [25]. Finally, the majority of adolescents in Western countries have access to the internet and make frequent use of internet technologies [26,27], which make web-based brief alcohol interventions particularly suitable for our target group.

### Objectives and hypotheses

The objective of the study described in this protocol is to evaluate the effectiveness of the What Do You Drink web-based brief alcohol intervention among heavy-drinking adolescents aged 15 to 20 years with a low educational background. A two-arm parallel-group randomized controlled trial will be conducted with two follow-up assessments (that is, after one and six months) to examine the effectiveness of the intervention. Two hypotheses will be tested. First, we expect that a larger percentage of participants in the experimental condition will drink within the normative limits of the Dutch National Health Council for low-risk drinking [28] when compared to the control condition as a result of the WDYD intervention. This means that participants’ consumption will not exceed a mean heavy alcohol use consumption of more than seven (girls aged 15 to 16 years), twelve (boys aged 15 to 16 years), fourteen (women aged 17 to 20 years) or twenty-one (men aged 17 to 20 years) glasses of standard units of alcohol per week and/or, in the case of binge drinking, five or more glasses of standard units of alcohol on one drinking occasion at least once per month and week for boys and girls aged 15 to 16 years and men and women aged 17 to 20 years, respectively, at one month and six months after the intervention. Second, we expect that participants in the experimental condition will reduce their mean weekly alcohol consumption and frequency of binge drinking. Thus, it is hypothesized that exposure to the WDYD intervention will be more effective compared to no intervention.

## Methods/design

### Trial design

The effectiveness of the What Do You Drink web-based brief alcohol intervention will be tested in a two-arm parallel-group cluster randomized controlled trial. Participants comprise approximately 750 heavy-drinking adolescents with a low educational background aged 15 to 20 years: 375 are in the experimental condition (web-based brief alcohol intervention) and 375 are in the control condition (no intervention).

### Procedure and participants

Participants will be recruited at VMBO and MBO institutions in the Netherlands. The VMBO and MBO institutions will be selected from a list of all educational institutions in different regions in the Netherlands. The selected educational institutions will receive an invitation letter with additional information about the study. A standardized cover story will be used in which institutions are informed that their students will participate in a study examining newly developed health education materials addressing alcohol use. After two weeks, the institutions will be contacted by telephone to establish whether or not they are willing to participate in the study. Those institutions that are willing to cooperate in the study will be asked to participate with as many as possible classes. Additionally, they will be requested to distribute letters to the parents of adolescents aged 15 to 16 years to inform them about the institution’s study participation. The parents will be given the opportunity to refuse participation by email or telephone during the entire study period. The informed consent materials will state clearly the expectations of frequency, duration and extent of study participation.

From the participating institutions, none of the adolescents will be excluded from study participation to avoid stigmatization and social exclusion. However, after the recruitment and enrolment of the institutions in the trial, an online baseline assessment will be carried out to establish whether the adolescents of the participating classes can be included in the study sample. Therefore, participants must: 1) be between 15 and 20 years old, 2) report heavy drinking in the past six months, and 3) be willing to change their alcohol consumption. Our definition of heavy drinking is based on measures of heavy alcohol use and binge drinking, which differs across participants’ sex and age. To fulfill the sample inclusion criteria, adolescents should be a heavy alcohol user and/or a binge drinker. However, problem drinkers who show symptoms of alcohol abuse or dependence (that is, an AUDIT score of 20 or above [29]) and/or of receiving treatment for alcohol-related problems will be excluded from participation since the WDYD intervention focuses on the prevention of heavy drinking rather than the prevention of problem drinking. The Ethical Committee (ECG) of the Faculty of Social Sciences of Radboud University Nijmegen in the Netherlands has approved the trial protocol.

### Intervention

Originally, the WDYD intervention had been developed for heavy-drinking young adults aged 18 to 24 years. Therefore, minor adaptations have been made concerning the usability (that is, use of language) of the intervention to make it more appropriate for the target group of adolescents with a low educational background aged 15 to 20 years. Detecting and reducing heavy drinking of adolescents who are willing to decrease their alcohol consumption is the main aim of the WDYD intervention. Motivational Interviewing principles [30] and parts of the I-Change model [31] are incorporated in the intervention, in which knowledge, social norms, and self-efficacy are embedded as the most changeable determinants of behavior change. To increase adolescents’ motivation to adapt their drinking behavior, discrepant personal information is presented [32]. Therefore, the first part of the WDYD intervention consists of a screening procedure and a form of personalized feedback based on the screening outcomes. The second part of the WDYD intervention focuses on goal-setting, action planning, and strengthening adolescents’ drinking refusal self-efficacy (for more details of the intervention see [33]).

### Intervention conditions

Participants in the experimental condition will be exposed to the WDYD intervention, while participants in the control condition will receive no further intervention.

### Data collection

The recruitment, enrolment in the trial, online baseline assessment, and randomization is scheduled during the period of October to December 2011. The follow-up assessments will be obtained one and six months after the intervention, that is, in the period November to December 2011 and April to May 2012. In addition, the participating VMBO and MBO institutions will be offered an incentive in the format of the DVD workshop ‘Advertisement agency’, after their students have completed the total follow-up period. The workshop, designed by the Trimbos Institute (Netherlands Institute of Mental Health and Addiction), is developed for adolescents and focuses on alcohol, tobacco, and drugs use and peer pressure. An overview of the measurements is given in Figure 1.

**Figure 1 F1:**
[figure not shown]
Study design.

### Outcomes

Primary outcomes measures are: 1) the percentage of participants who drink within the normative limits of the Dutch National Health Council for low-risk drinking, 2) reductions in mean weekly alcohol consumption, and 3) frequency of binge drinking. The secondary outcome measures include the alcohol-related cognitions, attitudes, self-efficacy, and subjective norms.

The Dutch version of the Alcohol Weekly Recall [34] will be used to measure participants’ average glasses of standard alcohol units in the previous week. To assess frequency of binge drinking, respondents will be asked how often they consumed five or more glasses of standard alcohol units on one drinking occasion at least once per month (boys and girls aged 15 to 16 years) and week (men and women aged 17 to 20 years) in the past month and week, respectively.

Attitudes towards alcohol use reflect the extent to which respondents have a positive or negative regard of alcohol use. Respondents will be asked about the perceived effects of alcohol (for example, ‘Drinking alcohol makes me feel less shy’ and ‘Drinking alcohol makes me fat’). Respondents will complete 10 positive and 10 negative attitude items and respond on a 4-point scale ranging from (1) ‘strongly disagree’ to (4) ‘strongly agree’.

Self-efficacy will be measured with a modified version of Young’s Drinking Refusal Self-Efficacy Questionnaire Revised Adolescents Version (DRSEQ-RA: [35,36]), which assesses respondents’ ability to resist drinking alcohol in various situations. This measure was modified by adding additional risk situations in which respondents find it hard to resist alcohol. Additional items were generated by the authors (for example, ‘When I have finished my exams’). Respondents will complete 26 items and respond on a 6-point scale from (1) ‘I am very sure I cannot resist alcohol’ to (6) ‘I am very sure I can resist alcohol’, with higher scores reflecting higher DRSEQ-RA. The measure incorporates three subscales that reflect drinking refusal self-efficacy relating to social pressure (for example, ‘When my friends are drinking’), emotional relief (for example, ‘When I am angry’) and opportunity to drink (for example, ‘When I am watching TV’).

Descriptive norms will be assessed by measuring perceived alcohol use among best friend, partner, parents, and typical same-sex student. Respondents will be asked about the frequency of their best friend’s/partner’s/parents’ and typical same-sex student’s alcohol use in the previous four weeks. The respondents can respond on a 6-point scale ranging from (1) ‘have not been drinking’ to (6) ‘every day’ [37]. The intensity of their best friend’s/partner’s/parents’/typical same-sex student’s drinking will be assessed by asking the respondents the number of glasses of standard alcohol units their best friend/partner/parents/typical same-sex student had drunk in the previous week in the contexts of at home and outside the home [38]. By asking about these four specific situations, respondents are forced to increase the reliability of response [39]. The scores on these four questions will be summed up to get an indication about the total number of glasses of standard alcohol units the best friends/partner/parents/typical same-sex student of each adolescent consumed in the past week.

Injunctive norms will be assessed by measuring the perceived acceptability of drinking among adolescent’s best friend, partner and typical same-sex student. Respondents will be asked: ‘Do you think that (1) your best friend, (2) your partner and (3) the typical same-sex student would mind if you drink a lot?’ Responses will be coded using a 4-point scale anchored by (1) ‘not at all’ to (4) ‘a lot’. A higher score indicates more liberal norms towards adolescent drinking. Thus, both proximal and distal reference groups will be used to assess social norms.

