### Sample size

The power calculation of our study reflects the notion that we aim to detect an increase in the percentage of participants showing low-risk drinking after one month of 42% in the experimental group versus 31% in the control group [40]. A total sample size of 750 respondents (n = 375 per condition) will be required to test the hypothesis in a two-sided test at alpha = 0.05, a power of (1-beta) = 0.80, and expecting a worst-case scenario of totally 15% loss-to-follow-up after randomization. The fact that the data are clustered (participants are nested in classes) was taken into account in the power calculation. The intraclass correlation is expected to be between 0.03 and 0.06 indicating that there is a low degree of similarity between participants within classes [41].

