### Statistical methods

Descriptive analyses will be conducted to explore whether the randomization has resulted in a balanced distribution of participants’ demographic characteristics across conditions. The potential non-independence of the clustered data, due to the fact that participants are nested in classes, will be taken into account in the analyses.

Data will be analyzed in accordance with the intent-to-treat principle and the completers-only framework in SPSS and/or Mplus. For the intention-to-treat analyses, missing data at follow-up assessments will be handled using multiple imputations using the predictive mean matching method (continuous data) and the logistic regression method (categorical data). Additionally, completers-only analyses will be conducted on participants with scores on all measurements.

Logistic and linear regressions will be performed in both the intention-to-treat and the completers-only analyses to test how the WDYD intervention is related to the alcohol outcomes (that is, heavy drinking, mean weekly alcohol consumption, and frequency of binge drinking) one and six months after the intervention. Besides testing the main effects of the WDYD intervention, moderating effects of age, sex, and drinking status will be investigated to establish whether subgroups are more likely to benefit from the WDYD intervention. Moreover, mediating processes will be examined to: 1) test whether the WDYD intervention modifies the mediating factors (that is, attitudes, social norms and self-efficacy: ASE-model [42]), 2) provide insights into how the WDYD intervention achieves its effects (that is, which mediating factors are modified by the WDYD intervention that are related to alcohol outcomes), and 3) reveal which mediating factors are the most important for realizing change in the alcohol outcomes [43]. Three steps will be performed to analyze the mediating effects [44]. First, it will be analyzed whether the WDYD intervention has an effect on the mediating factors. Then, the effects of the mediating factors on the alcohol outcomes will be analyzed, while controlling for the effect of the WDYD intervention. Finally, it will be analyzed whether or not the size of the mediated effects are statistically significant [44,45].

The study will be performed in accordance with the CONSORT (Consolidated Standards of Reporting Trials) guidelines [46].

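### Three unranked primary outcomes, each tested at one and six months, lead to one effectiveness conclusion, although the trial is sized for only one of the six comparisons

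*Protocol article*

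**What the plan says.** The Outcomes section (and the Abstract, in almost the same terms) lists the primary outcomes side by side. The list opens with "Primary outcomes measures are: 1) the percentage of participants who drink within the normative limits of the Dutch National Health Council for low-risk drinking". The remaining two items come in the same sentence, with nothing to rank them below or above the first: "2) reductions in mean weekly alcohol consumption, and 3) frequency of binge drinking". None is marked as leading.

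Statistical methods plans logistic and linear regressions for low-risk (there called heavy) drinking, "mean weekly alcohol consumption, and frequency of binge drinking) one and six months after the intervention". Neither follow-up is marked as primary.

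The same section describes two analyses: "Data will be analyzed in accordance with the intent-to-treat principle and the completers-only framework in SPSS and/or Mplus". It gives the missing-data method for intention-to-treat and then continues: "Additionally, completers-only analyses will be conducted on participants with scores on all measurements". All regressions are run in both.

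Objectives and hypotheses states two hypotheses. The first concerns low-risk drinking at both follow-ups. The second joins weekly consumption and binge frequency. Both lead to one overall statement of superiority over no intervention.

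Sample size is based on one comparison only, the percentage "showing low-risk drinking after one month of 42% in the experimental group versus 31% in the control group", with two-sided alpha 0.05, power 0.80 and 15% loss. This is the only place where an alpha is given.

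**The concern.** Three outcomes at two time points give six primary comparisons. The protocol does not say which one decides the trial, or whether one, some or all must succeed before the intervention is called effective. The choice could then be made after the results are known, and the 0.05 in the sample size section would not be the error rate of the trial's conclusion.

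The document also does not point consistently to a lead outcome. The sample size singles out low-risk drinking at one month, but the hypothesis repeated in the Abstract's discussion mentions only weekly consumption and binge frequency and leaves out the outcome on which the trial was sized.

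**Working it through.** **1. Reproduce the stated sample size.** Inputs from Sample size: p1 = 0.42, p2 = 0.31, difference 0.11, mean 0.365, two-sided alpha 0.05 (z = 1.960), power 0.80 (z = 0.842), loss 15%.

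- Without continuity correction: n = [1.960 × √(2 × 0.365 × 0.635) + 0.842 × √(0.42 × 0.58 + 0.31 × 0.69)]² / 0.11² = 299.5, so 300 per arm.
- With continuity correction: n' = (n/4) × [1 + √(1 + 4/(n × 0.11))]² = 317.4, so 318 per arm.
- After loss: 318/0.85 = 374.1, so 375 per arm and 750 in total.

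This matches the stated figure for one test at 0.05. Nothing in it is reserved for the other five comparisons. (The match also uses no design effect for classes, although the section says that clustering was allowed for. That is a separate question.)

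**2. Count the comparisons.** 3 outcomes × 2 time points = 6 in one analysis set.

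**3. Error rate if any one significant result suffices.** Two assumptions are needed that the document does not supply: each comparison is tested at two-sided 0.05, and the six test statistics are correlated normals. Independence gives 1 − 0.95⁶ = 26.5% two-sided and 1 − 0.975⁶ = 14.1% in the beneficial direction. Independence is unlikely: the first outcome is defined from weekly consumption and binge drinking, and the same pupils are measured twice. Simulation with no true effect (400,000 draws or more) gives the following. The first figure in each cell has one common correlation for all pairs. The second has that correlation between outcomes and between times, with the product of the two where both differ.

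| Assumed correlation | At least one p < 0.05, two-sided | At least one in the beneficial direction (nominal 2.5%) |
|---|---|---|
| 0.5 | 20.8% / 22.0% | 10.4% / 11.1% |
| 0.7 | 16.4% / 17.6% | 8.2% / 8.8% |
| 0.9 | 10.8% / 11.5% | 5.4% / 5.8% |

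**4. Error rate under stricter readings.**

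- All six must succeed: about 1% at correlation 0.9 and less below that, so no inflation.
- Two hypotheses, each requiring all its parts: at most 2 × 5% = 10% two-sided and 2 × 2.5% = 5% in the beneficial direction.

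**5. Effect of the completers-only analysis.** With an assumed correlation of 0.92 to 0.95 between the two analyses, the twelve results together give 27% to 29% (from 22.0%) at correlation 0.5, and 22% to 23% (from 17.6%) at 0.7. The second set adds about 5 to 7 percentage points.

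**The case against.** The strongest reply is that this is a condensed article, and that multiplicity adjustment, test order and success rules are commonly left to an analysis plan, which is not shown. That stands as far as it goes: a reader might infer that the trial has no error control at all, and the document cannot support that. What the document does fix is three unranked primary outcomes at two unranked time points, and this is the point made here.

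Further stronger readings are tempting and should not be adopted.

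- A reader might infer that the plan tests every comparison at 0.05. Alpha appears only in Sample size, for low-risk drinking at one month. Its use for the other five is an assumption.
- A reader might quote 26% as the error rate. That is the independence bound, which the construction of the first outcome makes unlikely. The two-sided figures also count significant harm. A false claim of benefit is measured by the beneficial-direction figures against 2.5%.
- A reader might treat the two analysis sets as co-equal and count twelve tests. Intention-to-treat comes first, with its own missing-data method, and the completers-only analysis is introduced as an addition. That hints at an order, though no label confirms it. The two sets also overlap heavily, so the independent figure for twelve tests, 46%, is not realistic.
- A reader might call sizing on one outcome an error. It is ordinary practice. What is missing is a statement that this outcome and time point lead.

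Finally, the two hypotheses could each be read as needing all their parts. The wording allows this but does not say so, and step 4 shows that even then the beneficial-direction bound is 5%, not 2.5%.

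**Conclusion.** The point holds in this form: six primary comparisons feed one conclusion of effectiveness, with no lead outcome, lead time point or success rule, while the sample size was computed for one of them. If any one result significant at 0.05 counts as success, the chance of at least one false positive is roughly 11% to 22% two-sided and roughly 5% to 11% in the beneficial direction, for assumed correlations of 0.9 to 0.5. These figures rest on the any-one-suffices reading, on 0.05 per comparison and on correlations that are not in the document, so the range should be quoted and not a single value. A requirement that all six succeed would remove the inflation, but none is stated. The completers-only analysis is a minor part of the problem. The change should be made, because it is simple and decides what the trial can claim.

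**What to change.** Name low-risk drinking at one month, by intention-to-treat, as the single primary test at two-sided alpha 0.05. It is the comparison in the sample size section, so multiplicity calls for no change to alpha or to the 750 participants.

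Make the other five comparisons secondary, or test them under a prespecified error-controlling procedure. A fixed sequence is one option. The document supports no particular order, so the investigators should choose it before seeing data. Label the completers-only analysis as a sensitivity analysis.

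The cost is wording. The other outcomes and the six-month results lose stand-alone confirmatory status, but are still estimated with confidence intervals.

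Keeping all six as equal primaries with a Bonferroni split (0.05/6 = 0.0083) would be dearer. With 375 × 0.85 = 318.75 completers per arm, no design effect and no continuity correction, power for the sized comparison would fall from 0.82 to 0.60. Restoring 0.80 would take 463/0.85, or 545 per arm.

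### Binge-drinking frequency, a primary outcome, is recalled over a month at ages 15–16 and a week at ages 17–20, and no common scale is fixed for its regression

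*Protocol article*

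**What the plan says.** All references are to the protocol article.

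- **Outcomes** names three primary outcomes; the second and third are "2) reductions in mean weekly alcohol consumption, and 3) frequency of binge drinking".
- For the third, "respondents will be asked how often they consumed five or more glasses of standard alcohol units on one drinking occasion". The same sentence then adds "at least once per month (boys and girls aged 15 to 16 years) and week (men and women aged 17 to 20 years" and sets the recall period as "in the past month and week, respectively".
- **Objectives and hypotheses** uses the same month/week split as part of the low-risk norm behind the first primary outcome: "on one drinking occasion at least once per month and week for boys and girls aged 15 to 16 years", with the week applying to ages 17 to 20. A separate second hypothesis expects lower weekly consumption and less frequent binge drinking.
- **Statistical methods** states that "Logistic and linear regressions will be performed in both the intention-to-treat and the completers-only analyses", for outcomes given as "heavy drinking, mean weekly alcohol consumption, and frequency of binge drinking". Beyond main effects, "moderating effects of age, sex, and drinking status will be investigated". Clustering by class is to be taken into account. The section does not assign a model type to each outcome and mentions no common period, offset or separate models by age group.
- Other items under Outcomes use one period for all ages. Own weekly consumption covers the previous week, and the frequency item on other people's drinking covers four weeks.

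**The concern.** An age-specific norm makes sense for deciding whether someone drinks within the limits. A frequency is a different kind of quantity: to be compared or averaged it needs one length of observation. Here the norm's month/week split appears to have been carried into the measurement of the frequency itself, so two participants with the same behaviour give different values if one is 16 and the other 17.

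The estimated treatment effect on a primary outcome could then have no interpretable unit. How much each age group contributes would depend partly on the questionnaire wording, and a difference in age mix between arms could look like a difference in drinking. The recall window is a measurement rule that this document states. An analysis plan could rescale the answers, but it could not recover the weeks that older participants were never asked about.

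**Working it through.** **What there is to reproduce.** The plan gives no rate, effect size or power for binge frequency and no age mix. Its sample size (375 per condition, 15% loss) is derived for low-risk drinking. There is no plan figure on this point, so the numbers below rest on stated assumptions.

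**Notation.** f = share aged 15–16; w = older group's weekly rate; r = younger-to-older ratio of weekly rates; k = window ratio; δ = proportional reduction, taken as equal in both groups.

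**Step 1: window ratio.** k = 28/7 = 4 for a four-week month, or 30.44/7 = 4.35 for a calendar month.

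**Step 2: unit, if the item is a count.**
- Linear main effect on the mixed counts: −δw[(1 − f) + f·k·r].
- True effect per week: −δw[(1 − f) + f·r]. The effect per month is k times this.
- With k above 1, the mixed coefficient equals the weekly effect only at f = 0 and the monthly effect only at f = 1.
- Example (w = 0.8, r = 1, δ = 0.2, f = 0.33): mixed = −0.16 × (0.67 + 0.33 × 4.35) = −0.337, against −0.16 per week and −0.16 × 4.35 = −0.70 per month.

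**Step 3: younger group's share of the coefficient.** Share = f·k·r / (f·k·r + 1 − f), with k = 4.35:

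| r | f = 0.10 | f = 0.20 | f = 0.30 | f = 0.50 | share exceeds half when f is above 1/(1 + k·r) |
|---|---|---|---|---|---|
| 1 | 33% | 52% | 65% | 81% | 19% |
| 0.5 | 19% | 35% | 48% | 68% | 32% |
| 0.25 | 11% | 21% | 32% | 52% | 48% |

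At r = 0.25, k·r = 1.09, so the share is close to headcount.

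**Step 4: chance age imbalance with no treatment effect.** If the share aged 15–16 differs by d between arms, the mixed mean shifts by d·w·(k·r − 1). With d = 0.05 and w = 0.8:
- r = 1: 0.04 × 3.35 = 0.134
- r = 0.5: 0.04 × 1.175 = 0.047
- r = 0.25: 0.04 × 0.0875 = 0.0035

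On the same mixed scale as the Step 2 example, 0.134/0.337 is about 40% of the effect.

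**Step 5: simulation.** Overdispersed counts, 375 × 0.85 ≈ 319 per arm, 2,000 runs, no clustering, f = 0.2, older weekly rate 1, 20% reduction in both groups.

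| r | Mixed windows | Rescaled to per week | One month for all |
|---|---|---|---|
| 1 | −0.34, power 0.50 | −0.20, power 0.67 | −0.87 per month, power 0.91 |
| 0.25 | −0.20, power 0.60 | −0.17, power 0.52 | −0.75 per month, power 0.82 |

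With no effect and r = 1, a 5-point age imbalance gave 13% rejections and a 10-point imbalance 42% on mixed windows. After rescaling, both were near 5%. Rescaling restores the unit but does not always gain power; a common month does better in both rows.

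**Step 6: yes/no reading.** The item joins a how-often question to an at-least-once threshold, and Objectives and hypotheses uses the same threshold as a yes/no criterion. If the variable is binary, the event is any binge in a month at ages 15–16 and any binge in a week at ages 17–20. Steps 2 to 5 then do not apply. The outcome becomes the binge component of the first primary outcome and no longer measures frequency.

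**The case against.** The strongest reply has five parts.

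1. **Pooling is not stated.** The article never says that both age groups enter one model, and a conversion could sit in a fuller plan. This stands as a caution. Still, one 15-to-20 sample with a main effect, and age named only as a moderator, strongly implies pooling.
2. **The item may be yes/no.** Logistic regression would then give an odds ratio, and the unit problem and the fourfold weight disappear. This also stands, but it replaces one defect with another (Step 6).
3. **Dominance of the younger group is not shown.** A reader might infer that the estimate is driven by ages 15–16. That needs an age mix and relative binge rates, and the document gives neither. Its lower binge threshold for the younger group makes equal weekly rates doubtful. The table supports only that over-weighting is possible.
4. **Age imbalance is chance, not bias.** Its expectation is zero under randomisation. Classes are allocated within institutions in blocks of four, and demographic balance is to be described. This stands. Allocating whole classes makes an age difference more plausible than individual allocation would if classmates are close in age, but that is an assumption. Dividing 0.134 by the weekly effect of 0.16 gives a tempting 84%, but this mixes two scales.
5. **Turning 17 during follow-up.** A reader might infer an artificial fall in counts as participants change window. If ages were uniform, 6/24 = 25% of the 15–16 group would turn 17 within six months. The document does not say that the item follows current age, and any switch would occur in both arms.

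**Conclusion.** The concern holds in limited form. Two recall windows differing about 4- to 4.35-fold by age are stated for a primary outcome, and no common scale is fixed for its regression.

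- **Count reading:** given pooling, the coefficient is neither per week nor per month at any age mix that includes both groups. Over-weighting of the younger group is possible but not established. Its 11% to 81% share rests on the assumed ranges (10–50% aged 15–16, rate ratio 0.25 to 1) and on an equal proportional effect. A chance age imbalance can shift the estimate, by almost nothing when the younger weekly rate is about a quarter of the older.
- **Yes/no reading:** the outcome is a different event by age and largely duplicates part of the first primary outcome.

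The documents do not support saying that the result is driven by the younger group, that the design builds in a spurious effect, or that participants will switch windows. The sample size, set on low-risk drinking, is not affected by this point.

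**What to change.** State whether the outcome is a count or binary. Ask every participant, at every wave, for the number of occasions with five or more glasses over one common window, for example the past month, and use that count as the frequency outcome. Keep the age-specific threshold only for classifying low-risk drinking.

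If the items are already fielded, analyse the counts with a log link, an offset for the recall length actually used and an age-group term, accounting for class clustering, and report a rate ratio. An age-group term alone in a linear model would deal with age imbalance but not with the missing unit. For waves not yet fielded, keep the same window for each participant throughout. The offset needs counts; if only a yes/no answer was recorded, describe the outcome as that and show it by age group.

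The cost is one changed questionnaire item, or one or two extra model terms. The analysis-only remedy restores a common unit but not the information lost by asking older participants about one week.
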